## Abstract

**Background:**

The high prevalence of non-communicable diseases places significant demands on the healthcare system. As a result, hospitals are seeking to broaden their role to include more integrated health promotion. Strong leadership at different levels of the organisation is required for the successful integration of health promotion in hospital settings. The status of surgeons within healthcare affords them significant influence over clinical practice, and by extension, institutional policy and practice. The voice of this professional group is, however, absent from preventative health literature. The aim of this research is to identify which health promotion activities surgeons undertake, and to explore the attitudes of the profession towards health promotion activities.

**Methods:**

A mixed methods study will be conducted, guided by the principles of sequential explanatory design. Quantitative results from a clinician survey will be followed by in-depth, semi structured interviews to explore findings in more depth through qualitative analysis. We will recruit from general and orthopaedic surgeons and registrars in a major tertiary hospital in a regional city in Australia (n ≈ 31). Data will be collected, independently coded and analysed using a qualitative descriptive approach. Quantitative and qualitative results will be merged during interpretation to provide complementary perspectives of interrelated contextual factors that influence health promotion activities amongst hospital surgeons.

**Discussion:**

The depth of insight gained from these highly professionalised clinicians will offer a distinctive perspective on current practice, as well as the challenges of implementing effective health promotion into surgical practice. The findings from this research will assist in guiding strategy and policy at both clinical and institutional levels on health promotion planning and practice. Gaining insights from surgeons will strengthen the evidence base to assist the integration of health promotion into hospital practice.

**Electronic supplementary material:**

The online version of this article (10.1186/s12913-018-3606-8) contains supplementary material, which is available to authorized users.

## Background

Chronic non-communicable diseases are the leading cause of illness, disability and death worldwide [1]. These diseases include cardiovascular diseases, chronic respiratory diseases, diabetes, and some cancers [1], and are largely preventable [2]. There are a number of key reasons behind the rise in chronic diseases, including increasing life expectancy, the ageing of the population and behavioural health risk factors [1]. Chronic diseases have an intricate association with modifiable lifestyle risk factors, such as physical inactivity, poor nutrition, and smoking [3]. The increased prevalence of non-communicable diseases over the past number of decades has influenced the demands that are placed on the health system [4]. Hospitals, as a result, have been required to broaden their role from their primary focus of disease treatment towards a position of more integrated health promotion and holistic care [5].

Hospitals are in a suitable position within the health care system to be advocates for health promotion [6]. Hospitals represent the primary concentration of health resources, professional skills and medical technology in the community [5]. The extensive resources that hospitals command mean that even a small shift of focus has the potential to bring about an increase in resources dedicated to health promotion [5, 6]. This shift, over time, could bring potential health benefits to the community [5, 7]. The hospital healthcare system also provides important opportunities to reach the most disadvantaged in the community, who are often hard to reach by wider population-based approaches [8]. Moreover, hospital-based clinicians are seen as credible sources of advice and expertise on health issues that extend beyond their responsibilities for services related to sick care and can be strong advocates for health promotion [7].

Surgeons have an important role within the hospital system in the promotion of healthy lifestyles and behaviour change for patients with, or at risk of, chronic disease [9]. Due to their extensive training, specialisation and medical expertise, surgeons are perceived as dependable sources of advice and expertise on health issues that extend beyond their responsibilities for services related surgical care [6]. Surgeons as such, are influential in the promotion of lifestyle behaviour change [7]. The surgical profession is one of responsibility and leadership, playing key roles in strategic planning, especially pertaining to clinical care [10]. Strong leadership at different levels of the organisation has been indicated as the key element for integrating health promotion in a hospital setting [7, 8]. Hospital surgeons therefore have significant influence over clinical settings, and by extension, institutional policy and practice, necessary for the implementation of research into clinical practice [10].

The persuasive role of hospital doctors in promoting health-related behaviour change has been acknowledged [11]. There is however, a significant gap between potential and practice, with low rates of preventive health interventions reported by hospital doctors [12]. Only a small proportion of emergency physicians reported routine screening and counselling of patients about preventive health; furthermore, the majority were not confident in their ability to assist patients change their health-related behaviours [13]. When surveyed, hospital speciality clinicians also felt that they were not the most appropriate person to offer patients advice about behaviour change [12]. The authors suggested that this result provides an explanation for the low implementation rates of behaviour change interventions in the hospital setting [12]; however, no interviews were carried out to further probe the survey findings to gain a deeper understanding of the topic. Decisions on implementing evidence into surgical practice have been found to be multifactorial [14]. These decisions are influenced by local, contextual and social circumstances [15, 16], as well as organisational processes and available resources [15, 16]. Given the prevalence of chronic diseases and the recommendation for hospitals to broaden their role towards a position of more integrated health promotion [5, 7, 8, 17], it is important to gain insights from hospital surgeons due to the influence that they exert on patient behaviour and clinical policy and practice. Existing literature has reported qualitative and quantitative findings separately rather than linking quantitative data of actual clinical practice to qualitative data on beliefs and attitudes that influence such practices [18]. Therefore, a better understanding of how attitudes towards risk factor management influence clinical practice is required to guide future preventive health policy and practice.

The aim of this mixed-methods study is to identify which health promotion activities surgeons carry out in public hospitals, and to explore the attitudes of the profession towards health promotion practice. Combining quantitative data on levels of risk factor intervention with qualitative data about beliefs and attitudes will highlight ways in which interventions and practice can be implemented in clinical care to increase the overall rate of risk factor management. The depth of insight gained from the study of these highly professionalised clinical groups will offer a distinctive perspective on current practice, and the challenges of implementing effective health promotion into hospital settings. The results of this study have potential to guide health promotion policy and practice into the future.

## Methods/design

This study will use a mixed methods approach to explore which health promotion activities surgeons carry out in public hospitals, and to understand attitudes of surgeons towards health promotion activities. Quantitative data will be derived from a clinician survey. Semi-structured interviews will be used to obtain qualitative data. The mixed methods study will use a sequential explanatory design [19]. This is a two phase design where quantitative data are collected prior to the collection of qualitative data. The sequential explanatory design uses the qualitative results to further explain and interpret the findings from the quantitative component. The study framework is grounded in pragmatic epistemology [20, 21], to explore clinician views, behaviours and actions relating to preventive health practice. To promote transparency of our planned research, Table 1 presents qualitative research design aspects within the COnsolidated criteria for REporting Qualitative (COREQ) studies framework [22].

**Table 1 Tab1:** Qualitative study design

Domain 1: Research team and reflexivity	
Personal characteristics	
1. Interviewer/facilitator	All interviews will be conducted by the same member of the study team.
2. Credentials	The interviewer will be a masters-level trained research assistant.
3. Occupation	The interviewer will be employed full-time as a project officer.
4. Gender	The interviewer will be male.
Relationship with participants	
6. Relationship established	Potential interviewees will be contacted with a standardised recruitment email to introduce the study and the interviewer and to request their participation.
7. Participant knowledge of the interviewer	The recruitment email will explain the study goals and why the interviewer is interested in conducting this research. This information will be reviewed at the start of each interview.
8. Interviewer characteristics	The recruitment email will provide information about the research team, including the interviewer. This information will be reviewed at the start of each interview.
Domain 2: Study design	
Theoretical framework	
9. Methodological orientation and theory	The qualitative portion of the study will use a qualitative description approach.
Participant selection	
10. Sampling	Potential interviewees will be selected based on their practicing status in the target hospital.
11. Method of approach	Potential interviewees will be approached with a standardised recruitment email.
12. Sample size	We anticipate conducting 5 to 10 interviews.
13. Non-participation	We will document any reasons provided by those who decline to participate as well as any individuals who do not respond to our recruitment email.
Setting	
14. Setting of data collection	Data will be collected via interviews conducted in person.
15. Presence of non-participants	We anticipate that the interviewer and interviewee will be the only individuals present.
16. Description of sample	The sample will include Orthopaedic and General surgeons and their registrars consulting out of the target hospital.
Data collection	
17. Interview guide	The interview guide will be developed by the study team. It will be pilot-tested and refined before data collection begins.
18. Repeat interviews	We do not anticipate conducting repeat interviews.
19. Audio/visual recording	Once permission is granted, interviews will be audio recorded.
20. Field notes	The interviewer will draft summary notes immediately after concluding each interview.
21. Duration	We anticipate that interviews will last no more than 30 min.
Domain 3: Analysis and findings	
Data analysis	
24. Number of data coders	We plan to have two coders pilot a sub-sample of transcripts. Once discrepancies are resolved and the codebook is finalised, the full set of transcripts will be coded by one individual.
25. Description of the coding tree	We plan to develop a coding tree (i.e., codebook) based on a review of the literature, a priori knowledge within the study team, and summary notes from interviews.
26. Derivation of themes	Themes will be derived once data have been coded. Preliminary themes may be identified based on discussions with the interviewer and review of field notes.
27. Software	We plan to use NVivo qualitative research software.
28. Participant checking	A bulleted list of key findings will be shared with participants once data have been coded and analysed.
Reporting	
29. Quotations presented	Quotations from interviews will be used to present findings, and they will be accompanied by an interviewee identification number.
30. Data and findings consistent	Our planned use of quotations will allow for assessment of consistency between our data and findings. We will also create supplemental tables with additional quotations to share as much information as possible when presenting our findings.
31. Clarity of major themes	We plan to use sub-headings listing our major themes to promote clarity when writing up our findings.
32. Clarify of minor themes	We plan to provide quotations from interviewees who raised minor themes or shared information contrary to findings of our major themes.

### Clinician survey

Surgeons will be invited to complete a short 17-item self-administered clinician survey to assess health behaviour risk factor management, perceived knowledge, confidence and attitudes towards preventative health (Additional file 1). The clinician survey asks respondents to report on proportions of clients seen over a recent period who they: (1) asked about smoking, nutrition, alcohol and physical activity; (2) assessed for readiness to change; (3) provided verbal and written advice on these risk factors and; (4) referred to other services for support in changing risk factors. These clinician practices are the dependent variables. The clinician survey also questions the participants about their knowledge and confidence in screening and managing each risk factor. In addition, attitudinal measures will be included for: (1) the clinicians’ opinion on the perceived effectiveness of the interventions; (2) the perceived importance of the intervention for the clients they see; (3) perceived work priority; and (4) perceived acceptability on the part of the client of raising the topic of lifestyle risk factors. The answers to these questions constitute the independent variables. All clinician survey items are measured on a 5-point Likert scale. The clinician survey has been adapted with permission from a previously developed instrument used to assess health behaviour risk factor management practices and capacity in community dwelling participants [18, 23].

### Semi- structured interviews

Qualitative data permits the recording of first-hand accounts of the individuals studied, offering rich, straight descriptions of experience or events [24, 25]. Following analysis of the clinician survey, semi-structured interviews will be conducted with a purposeful sample of surgeons and surgical registrars. Interviews will be structured in an attempt to gain participant’s opinions on factors that influence their decisions to undertake health promotion activities. Interviews offer value in understanding the perspective of individuals as well as the rationale for their actions [26]. The interviews will take place face-to-face where possible, with telephone interviews used where required for practical reasons.

This research will use qualitative description as the theoretical framework for the qualitative component [27]. Qualitative description provides straightforward, rich descriptions of experiences or events. Unlike other qualitative approaches which seek to develop new concepts or theories, the final outcome of qualitative description is a description of a participant’s’ experiences in a language similar to the participant’s own [27]. In qualitative description interviews are typically designed to focus on areas in health care that are either poorly understood and/or potentially amenable to intervention [27].

To facilitate uniformity, open-ended questions as well as question-related probes will be drafted. These questions will be designed to fit with the objectives of the research; however, they will not be finalised a priori, rather, they be will be built from the analysis of clinician survey answers [21]. Interview questions might be altered and adapted to differ between different groups of surgeons given the heterogeneity of the patients they see. Pilot interviews will be undertaken and audiotaped. The resulting interviews will be transcribed verbatim and used to refine the interview script. In keeping with the qualitative description framework, the interview script will be developed and amended formatively, based upon findings and emerging concepts [24, 28].

Descriptive information, such as years of practice and specialisation level, will be captured at the outset through the clinician survey. All participants will be encouraged to express opinions understanding that every answer is valuable and of use in the analysis [24, 29]. Full interviews will be audiotaped and transcribed verbatim. Field notes will be used to supplements audio and transcripts. After each interview the questions and answers will be assessed and reviewed to establish how well the interview script facilitated exploration of the topic. Where required, the script will be revised prior to the next interview [29].

### Ethics

The study has been approved by the Research Ethics Committees of the governing Hospital and University. Participants will choose to complete the clinician survey online or in hard copy. Participants who choose to complete the online version of the survey will be informed electronically, prior to commencing the survey that if they continue and complete the survey they agree to provide informed consent. Participants who choose to complete a hard copy version of the clinician survey will be given a Participant Information and Consent Form to complete prior to undertaking the clinician survey, as well as a stamped addressed envelope to return the consent form and clinician survey. Participants who choose to complete a hard copy version of the clinician survey will be reminded not to place their name on the clinician survey. Participants will be notified that their involvement is voluntary and can be withdrawn at any time, and that confidentiality is protected through the anonymization of all collected data. Any publication will not attribute specific comments to identifiable participants.

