### Participants

The target participants for this study are general and orthopaedic surgeons, and their registrars who consult out of the elective outpatient clinic in a major tertiary hospital in a regional city in Australia. The clients presenting to this clinic are ambulatory, non-admitted clients. While this group may be seen as a representation of the general community-dwelling population, research indicates that patients presenting to hospital clinics are more likely to have higher rates of chronic disease than the general population [3, 4, 7].

As there are only a limited number of surgeons (general and orthopaedic) (*n* = 20) and registrars (*n* = 11) operating out of the study hospital, we will offer participation to all of these practitioners. Recruiting all surgeons and registrars consulting out of the hospital will increase the potential sample size, and provides a participant sample with differences in career stage and level of training. In qualitative description, the methodology seeks to gather enough data to saturate the explanation [27, 28]. Interviews will be continued until no interviewees are providing new information, and data saturation is determined [30]. If it is deemed that theoretical saturation is reached prior to full recruitment, then recruitment will discontinue [25, 27, 30].

We will recruit participants from one study site only. We have chosen to recruit participants from one study site only due to the heterogeneity that exists between hospitals in terms of infrastructure, clinical practice and resources, as well as broader contextual factors that may differ between areas serviced by hospitals such as the availability of, and access to, local preventative health providers and programs [31]. This study is part of a broader body of work, investigating health promotion in non-admitted secondary care patients. We have already undertaken a clinical trial investigating behaviour change interventions for non-admitted secondary patients in a single-hospital setting (ANZCTR trial id: ACTRN12616001331426). This proposed mixed-methods study aims to fill the gap in knowledge pertaining to surgeons’ actual involvement in the practice of health promotion in an ambulatory care setting; these results can be used in the design of subsequent clinical trials involving surgeons screening and recruiting secondary care patients for behaviour change interventions.

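### Paper respondents post the consent form and the unnamed survey back in one envelope, so their answers can be linked to a person on receipt

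*Protocol article*

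**What the plan says.** All the relevant procedure is in the Ethics section of the protocol article. The respondent picks the mode: "Participants will choose to complete the clinician survey online or in hard copy".

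- **Online.** Respondents are told on screen that "if they continue and complete the survey they agree to provide informed consent". No separate form is described.
- **Hard copy.** Respondents "will be given a Participant Information and Consent Form to complete prior to undertaking the clinician survey", and receive "a stamped addressed envelope to return the consent form and clinician survey". The envelope is singular and serves both documents. The same respondents "will be reminded not to place their name on the clinician survey".
- **Assurance given to everyone.** Participation can be withdrawn at any time, and "confidentiality is protected through the anonymization of all collected data". Publications will not tie comments to identifiable people.

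The article describes no second envelope and no step that parts the form from the survey on arrival.

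**The concern.** Asking for no name on a survey is useful only if the returned sheet should not show who filled it in. Sending it back with that person's completed consent form removes much of the benefit, because the two can be paired when the envelope is opened.

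This bears on data quality because the survey's dependent variables are clinicians' own reports of how many of their clients they asked, assessed, advised and referred (Clinician survey section). Such answers can drift towards the favourable when the respondent believes they are identifiable. The setting adds to that: one hospital, a small group who know each other, and invitations and reminders sent through the head of department (Recruitment section). The scores then sort clinicians into low, moderate and high implementers by quartile, and the survey results shape the interview questions (Analyses section), so any distortion would carry forward.

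**Working it through.** The plan states no figure on this point to reproduce. The check is a comparison of the two modes, followed by a look at whether the effect can be sized.

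**1. The two modes side by side (Ethics section)**

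| Step | Online | Hard copy |
|---|---|---|
| Who chooses the mode | Respondent | Respondent |
| Consent | By continuing and completing | Separate form, completed beforehand |
| Return | Electronic | One envelope, form and survey together |
| Reminder to omit name | Not described | Yes |
| Separation of consent from answers | No form described | Not described |

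The hard-copy column has the conflict: a reminder to omit the name, and a return route that delivers the survey with the form. Linkage on receipt follows if the completed form bears a name or signature. The article does not say that it does, so this is an assumption.

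**2. Is the online mode free of identifiers?** The article does not say so. The Semi-structured interviews section states: "Descriptive information, such as years of practice and specialisation level, will be captured at the outset through the clinician survey". That applies to both modes. The pool in the Participants section is 20 surgeons + 11 registrars = 31 clinicians. Years of practice combined with level could single out some of them without any form. The modes therefore differ in one documented respect, the form that travels with the answers. The article does not show one mode to be identifiable and the other anonymous.

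**3. Can the effect be sized?** Let *p* be the share of respondents using paper and *d* the rise in their mean score caused by feeling identifiable. The overall mean would shift by *p* × *d*.

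- *p* is not given. With 31 invited, paper returns could number anywhere from 0 to 31, so *p* lies between 0/31 = 0 and 31/31 = 1.
- *d* is not given, and nothing in the article allows it to be derived.

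The shift lies somewhere between 0 and *d*, with *d* unknown. No number can be put on it.

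**4. Sensitivity of the grouping.** If all 31 responded, an extreme quartile would hold 31/4 = 7.75, or about 8 clinicians, and fewer with a lower response. Groups of this size are sensitive to the placing of individuals. That shows why small distortions matter here, but not that any would occur.

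**The case against.** The strongest reply is that the plan does not contradict itself. It promises confidentiality through anonymising what has been collected, and that can be done after receipt: once the form is detached, an unnamed sheet remains. Nowhere does it promise that the team will never see who returned a survey. A separation step is a handling detail that an article may leave to the full protocol or the ethics application, and the committees of both hospital and university approved the study. Online also looks like the main route, since the invitation email carries the link and both reminders repeat it. A clinician uneasy about a form can use the link.

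Much of this stands. A reader might infer that the stated anonymity is defeated. The documents do not support that, because anonymity at the point of return was never stated. A reader might also infer that online respondents are spared any pressure to give favourable answers. That is not shown either, since the online survey is not said to be free of identifiers and collects the same descriptive items. Nor can a standard-deviation shift or a percentage of misclassified clinicians be claimed without inventing its inputs. It also goes too far to say that a mode effect could never be examined: paper comes by post and online electronically, so scores can be described by mode, although self-selection would limit what such a description shows.

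What does not stand is the view that this is only missing detail. The single envelope is a described procedure, and it sits beside an instruction that it weakens.

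**Conclusion.** The point holds as a minor flaw in procedure. As described, hard-copy surveys can be linked to a person on receipt, which undercuts the reminder to leave the name off, and the online mode has no described counterpart to the form. This rests on two assumptions: that the completed form carries a name or signature, and that form and survey are not kept apart by a safeguard described elsewhere.

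The effect on the data is a plausible risk of socially desirable reporting in the practice scores. It is neither demonstrated nor quantifiable from the article. If few or no clinicians choose paper, it will be negligible. It does not amount to a breach of the confidentiality promise or a reason to doubt the study's design.

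**What to change.** In the Ethics section, give paper respondents two envelopes, one for the consent form and one for the unnamed survey. Alternatively, use consent by completion on paper as is already done online; that changes an approved procedure and would need the ethics committees' agreement.

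In either case, record the mode of completion for every survey and describe the practice scores by mode, noting that respondents chose their mode.

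Add a code made up by the respondent to the survey. Without it, a separated survey could not be found again if its author withdrew, and the plan promises withdrawal at any time. The code would also allow a survey to be linked to an interview where that is wanted, without using the consent form.

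The cost is one extra envelope per paper respondent, or a small amendment to the consent procedure. The trade-off is that a consent form can no longer be matched to a particular survey except through the code.
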